#### Strategies to improve adherence to interventions {11c}

OptiMAT will send daily reminders for participants to log their daily self-monitoring assessment. Additionally, study staff will review mean OptiMAT use (percent days per month) at each of the participants’ monthly follow-up visits and provide strategies to maintain consistent OptiMAT use.

#### Relevant concomitant care permitted or prohibited during the trial {11d}

No concomitant care is prohibited during the trial.

#### Provisions for post-trial care {30}

Participant outcomes will be monitored for 6 months post study enrollment. However, participants in the MOUD+OptiMAT arm will be permitted to continue using OptiMAT until study closure. This study offers no compensation to those who suffer harm from trial participation.

#### Outcomes {12}

##### Primary outcome

The RCT has one primary outcome variable: percentage of clinically acquired urinalysis tests negative for opioid misuse. Urinalysis drug testing will consist of solid-phase enzyme immunoassay with positive tests analyzed by LC-MS for metabolite quantification. Urinalysis will assess opioid misuse, defined as presence of opioids in the urine other than Suboxone and its metabolites, including methadone, fentanyl (11 metabolites), oxycodone, phencyclidine, propoxyphene, and buprenorphine or norbuprenorphine, as well as other drugs of abuse including amphetamines, barbiturates, ethanol, benzodiazepines, THC, and cocaine (benzoylecgonine). Urinalysis drug tests will be acquired at each clinical visit, which occur weekly when participants initiate treatment but may occur less frequently (e.g., every 2 weeks) as participants maintain sobriety. We will calculate percent negative urinalysis tests out of total possible urinalysis tests to generate a Treatment Effectiveness Score (TES) describing participant outcome relative to other participants in the RCT [22]. Note that TES treats missed urinalysis tests as positive urinalysis results, thus accounting for treatment cessation. TES also accounts for the frequency of urinalysis tests, which varies as patients matriculate from phase I (weekly) to phases II–IV (biweekly to monthly) as patients demonstrate continued abstinence from opioid misuse.

##### Secondary outcome

The RCT will have several secondary outcome variables: self-reported days of opioid misuse, time to opioid lapse, and time to treatment discontinuation. Self-reported days of opioid misuse will be assessed using the TimeLine Follow-Back Calendar (TLFB) [23]. The TLFB is a calendar that provides cues (such as holidays) to prompt participants to recall days of opioid misuse over the past month. TLFB will be administered at study enrollment (baseline) and monthly by phone to record opioid misuse over the 6-month RCT. TLFB offers more granularity for days-per-month of opioid misuse than a quantitative urinalysis test but is subject to misreporting. Days of opioid misuse will be collected monthly in the 6-month study.

##### Tertiary outcome variables

We will also conduct survival analyses to determine if time to opioid lapse (from quantitative urinalysis results) or time to treatment discontinuation (from clinical records) differs between study arms. Finally, participants in the MOUD+OptiMAT arm will participate in qualitative interviews at month 2 about their OptiMAT usage including preferred features. We will evaluate if OptiMAT usage patterns (from quantitative smartphone data collected or the qualitative interviews) predicts opioid misuse in the MOUD+OptiMAT arm, as described below.

#### Participant timeline {13}

Participants will participate in the study for 6 months. Table 1 summarizes the method and timing of data collection.

**Table 1 Tab1:**
[figure not shown]
Method and timing of data collection

*Includes BIRC Demographic form, clinician report of comorbid alcohol or marijuana use, Alcohol Use Disorders Identification Test, Cannabis Use Disorders Identification Test, PROMIS Pain Interference Short form v1.0 4a

**MOUD+OptiMAT arm only

#### Sample size {14}

As brief interventions, smartphone apps have large effect sizes (Cohen’s *δ*) for aiding weight loss (δ ≥ 0.60), but weaker effects for aiding smoking cessation (*δ* ≈ 0.16–0.28) and alcohol reduction (*δ* ≈ 0.23-0.40) [9, 24–26]. Our pilot OnTrack study suggested similar effect sizes for reducing alcohol and marijuana use (both *δ* ≈ 0.26) and greater effect sizes for reducing risky sexual behavior (*δ* ≈ 0.70) [21]. A clinical trial using the CHESS-A smartphone app for reducing opioid misuse estimates an effect size for reducing opioid use of *δ* = 0.35, which is comparable to reducing use of other drugs of abuse. Assuming Cohen’s *δ* = 0.35, 1:1 randomization into the two study arms, a type I error rate of 0.05 for comparisons of the mean difference between the two groups using independent *t*-test, a statistical power of 0.80 could be achieved with accrual of *N* = 260 participants. Assuming a 20% drop-out rate and stratification of random study arm assignment across 12 variable levels (up to 3 recruitment sites × 2 chronic pain levels × 2 levels of comorbid use of marijuana or alcohol), this accrual goal could be reached with enrollment of 336 participants.

At this time, there is insufficient effect size and variance data to conduct an informed power analysis for using GEMA to support location-based intervention. We will report post-hoc effect sizes from data acquired from this project.

#### Recruitment {15}

We have obtained a partial waiver of HIPAA authorization so that clinical staff may identify patients meeting eligibility criteria and introduce those individuals to an on-site research coordinator. Recruitment and enrollment will be conducted by research staff rather than clinical staff to avoid coercion. The research coordinator will provide patients with IRB-approved advertisements describing the study. The research coordinator will also schedule an intake visit for interested patients, where patients will undergo the informed consent process (including full HIPAA authorization) in a private and confidential setting. We will also obtain a partial HIPAA waiver to allow undecided participants to provide us with contact information (i.e., name and phone number) so that we may recontact them later. Patients who provide written informed consent to participate in the study will be randomized into one of two intervention arms (see the “Assignment of interventions: allocation” section).

### Assignment of interventions: allocation

#### Sequence generation {16a}

Randomization of participants into study arms (MAT+OptiMAT or MAT-only) will be stratified by two variables: chronic pain and comorbid use of alcohol and/or marijuana, to address the possibility that these variables may influence treatment outcomes. Chronic pain is prevalent in this population, with 40% of our pilot participants reporting that pain has moderate or severe interference with daily activities (PROMIS Pain Interference Short form v4a). Patients receiving MOUD who have comorbid alcohol or marijuana use are placed on a slower progression from phase I to phase II to reduce potential misuse of take-home Suboxone. Chronic pain will be defined by pain intensity (none/low vs. moderate/severe on PROMIS Pain Interference Short form v4a), and comorbid alcohol or marijuana use will be defined as yes vs. no, as reported by clinical staff. We will document severity of alcohol or marijuana misuse with the Alcohol Use Disorders Identification Test (AUDIT) and Cannabis Use Disorders Identification Test (CUDIT) but will rely on clinical staff report for randomization. Randomization within each of the four strata (low pain + no comorbidity; low pain + comorbidity; high pain + no comorbidity; high pain + comorbidity) will be determined at study initiation by 1:1 allocation ratio using R software package blockrand which can be used to produce randomization lists and cards.

#### Concealment mechanism {16b}

The randomization order for each site will be written on notecards; sealed in opaque, consecutively numbered envelopes, and placed sequentially in a lockbox at each site.

#### Procedure for unblinding if needed {17b}

N/A. Only clinical (laboratory) staff and the biostatistician are blinded. We foresee no circumstances in which unblinding of these staff and investigator are permissible.

### Data collection and management

#### Plans for assessment and collection of outcomes {18a}

The primary outcome variable, quantitative urinalysis drug testing, will be acquired and analyzed by clinical staff per standard clinical procedure (see the “Primary outcome” section).

The secondary outcome variable time to opioid lapse will be derived from quantitative urinalysis drug test results above. The secondary outcome time to treatment discontinuation will be calculated from clinical staff as the first of three consecutively missed clinical appointments. The secondary outcome self-reported days of opioid misuse will be calculated from the monthly time-line follow-back calendar assessments, collected via phone by research staff.

#### Plans to promote participant retention and complete follow-up {18b}

Study staff will contact participants by text and phone throughout their 6-month participation in this study. Clinical sites include peer specialists (patients in long-term recovery from opioid use disorder) who serve as liaisons between the clinics and patients to provide support and guidance while encouraging recovery. Peer specialists also provide appointment reminders and encourage accountability in attending clinical visits.

#### Data management {19}

These data will be stored in patients’ electronic medical records (EMRs). All other surveys and instruments will be administered by research staff using REDCap (Research Electronic Data Capture) database, a secure web-based database for collecting and storing survey-based research data [27]. REDCap includes logic to detect incorrect data entry such as range check for data values. Research staff will manually enter urinalysis results from EMRs into REDCap with double data entry. For privacy and confidentiality, the REDCap database will store information by coded study ID without PHI linkages.

#### Confidentiality {27}

Not applicable: no identifying images or other personal or clinical details of participants are presented here nor will be presented in reports of the trial results. Informed consent materials are attached as Supplementary materials. Relevant protections from Supplementary materials against the loss of confidentiality are re-iterated in the “Protection against loss of confidentiality” section.

##### Protection against loss of confidentiality

OptiMAT assessments: The OptiMAT app will serve as a portal to a secure database storing all data entered by the participants. Any data entered into the OptiMAT app will be uploaded by secure HTTPS connection to a HIPAA-compliant, HITRUST-certified secure database managed by Enqbator. If the smartphone is on a secure private wireless network (like their home network or their provider’s cellular network), then the entered data will automatically upload to the server. If the smartphone is not on a secure private wireless network (e.g., a public network, like at a coffee shop), then the data will be stored on the phone locally until the smartphone is connected to a private wireless network or cellular network, at which point it will be automatically uploaded to server. This transfer process will happen automatically. Second, the participant will always be able to delete the OptiMAT app to prevent loss of confidentiality without losing data collected on the server. Third, study staff will require participants to enable passcode protected lockscreens on their phones and warn them about potential loss of privacy if they disable the passcode protected lockscreens. Finally, OptiMAT will store data using only study codes (no PHI) to further protect privacy and confidentiality.

Enqbator server and data access: Enqbator retains no rights to the study data uploaded to its server. At the conclusion of this study, the PI will download all study data from the Enqbator’s server, and Enqbator will delete the data on the server. All data on Enqbator server will be stored using study ID. The only potentially identifying information on the server is GPS location, which may be used to infer a home address or work address. Enqbator and UAMS have entered into a Master Services legal agreement specifying that Enqbator will “keep the Disclosing Party's (UAMS) Confidential Information confidential and will not use or disclose such information to any third party for any purpose except (i) as expressly authorized by the Disclosing Party in writing or (ii) as needed to fulfill the Receiving Party’s obligations under this Agreement.”

In-person assessments: To protect the identity of research volunteers, identifying contact information would be stored in a file (electronic) or in a locked cabinet (paper consent forms) separate from experimental data forms. All experimental data would be de-identified using an alphanumeric study code rather than a name or other identifying information. All data collection forms would be stored in a locked cabinet in the in a key card-protected room in the BIRC. Computer data records would be stored in password-protected network drives accessible only by study personnel. Data would be stripped of all identifiers, including the stripping of facial features from the anatomical MRI data. As a further measure to protect against the compelled disclosure of personally identifiable information, the investigative team has a NIDA-supported *Certificate of Confidentiality*. All personnel involved in the conduct of the proposed research would comply with the applicable Federal regulation for the protection of human subjects or, if no such federal regulation is otherwise applicable, they would comply with 45 CFR Part 46.

UAMS IRB policy considers all study personnel as mandated reporters, requiring that study personnel report incidents of child abuse and neglect to the Arkansas Department of Human Services. Study personnel must also report intentions to hurt others to local authorities. Subjects will be informed of this during the consent process and that incidents of child abuse/neglect or intentions to harm others are not covered by the Certificate of Confidentiality.

#### Plans for collection, laboratory evaluation, and storage of biological specimens for genetic or molecular analysis in this trial/future use {33}

Urine specimens will be collected for quantitative urinalysis of opioid misuse. Note that these urine specimens are collected by clinical staff as part of routine clinical care and are not collected specifically for this trial. Urinalysis results will be recorded in participants’ medical records and shared with research staff per study protocol (see Supplementary materials). Urine samples are destroyed following quantitative urinalysis.

### Statistical methods

#### Statistical methods for primary and secondary outcomes {20a}

##### Analyses of primary and secondary outcomes

The adequacy of randomization will be assessed by comparing baseline variables with known prognostic importance between the MOUD+OptiMAT and MOUD-only study arms. These baseline variables include demographic variables (age, sex, etc.) and clinical variables (Suboxone dose at initiation, initiating MOUD in a residential setting prior to initiating outpatient MOUD, etc.). An imbalance between the study arms is suspected if the proportion of variables with significant differences (*p* < 0.05) exceeds 5%. We will then run the statistical models below with and without those variables identified as being associated with imbalance between the groups included and compare the results. If the results from both approaches are similar, we will use the models without those variables included. Otherwise, we will adjust those variables in the models.

We will next assess missing data. If the percentage of missing data is large, multiple imputation will be performed if the missing pattern is missing at random. If the pattern is not missing at random (NMAR), other methods like Bayesian models will be used. Distributions of outcome variables will also be assessed using appropriate tests and visual graphs. Linearity between continuous covariates and outcomes will be checked and other functional forms of the covariates will be used if the linear relationships are not shown.

General linear or generalized linear models (GLMs) will be used to examine associations between study arms and primary outcome (percent negative urinalysis tests) at the 6-month endpoint depending on whether the outcome is normally distributed or not. The model will include the indicator variable for study arm (MAT+OptiMAT vs. MAT-only) and the three stratification variables used for randomization (Site, Chronic Pain, and comorbid Alcohol or Marijuana Use) only first. Then, the model will be run again with any additional covariates that were identified as being unbalanced between the study arms, and results will be compared.

For the secondary outcome of days-per-month of opioid misuse over the course of the 6-month study period, we will use generalized linear mixed models (GLMMs) to account for multiple records within each participant with Poisson or negative binomial distribution specified (as the outcome is probably skewed). GLMM will allow us to examine if overall days-per-month of opioid misuse varies between study arms and if this difference varies by study month. The models will include the indicator variable for MAT+OptiMAT vs. MAT-only, time with values 1 to 6 representing each of the six outcome variables measured monthly, time by study arm indicator interaction, strata variables and baseline days of misuse without and with additional covariates identified above added. The results from both models will then be compared.

If the percentage of missing data is deemed large and missing is not at random (MNAR) or if the planned sample size is not met, we will then use Bayesian methods for the analyses as Bayesian methods are more robust for small samples and can handle MNAR data by modeling the missing values. Posterior mean parameter ratios and posterior probabilities of the mean parameter ratios in the log scale being positive will be calculated. Bayesian models will include the models for outcomes and the models for indicator variables for missing values. The same variables as described in the previous paragraphs will be included. For the secondary outcome of days-per-month of opioid misuse, models will be fit separately for days of opioid misuse at each month with corresponding models fitted for the missing outcomes. Non-informative priors will be specified for all parameters. Convergence diagnostics tests such as Geweke, Raftery-Lewis, Heidelberger-Welch, Effective Sample Size, and posterior autocorrelations will be used to evaluate Markov chain convergence. Visual trace plots will also be used to aid evaluation of Markov chain convergence.

Survival analyses will be performed using the Kaplan-Meier method to compare the study arms on secondary outcomes (1) time to opioid lapse and (2) time to treatment discontinuation. Loss to follow-up will not be coded as relapse and will thus be censored in the Kaplan-Meier survival analyses for opioid lapse but will be coded as treatment discontinuation. As with the analysis above, stratification variables (Site, Chronic Pain, and Comorbid Alcohol or Marijuana Use) will be included in the survival analyses only first. Then, covariates identified above will be added and results will be compared. All analyses will be performed using SAS 9.4.

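### The final primary model is settled by baseline significance tests and an undefined comparison of treatment results, and baseline opioid misuse is left out of the prespecified primary model

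*Protocol article*

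**What the plan says.** All of the model-selection text is in the protocol article under Statistical methods for primary and secondary outcomes {20a}.

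- **Trigger.** Baseline variables believed to be prognostic are tested between arms: "An imbalance between the study arms is suspected if the proportion of variables with significant differences" at p<0.05 exceeds 5%. The list is open-ended. It names age, sex and "clinical variables (Suboxone dose at initiation, initiating MOUD in a residential setting prior to initiating outpatient MOUD, etc".
- **Two runs.** "We will then run the statistical models below with and without those variables identified as being associated with imbalance between the groups included".
- **Choice.** "If the results from both approaches are similar, we will use the models without those variables included". The alternative is "Otherwise, we will adjust those variables in the models". No criterion for similarity is given, whether on the estimate, the interval or the p-value.
- **Primary model.** The first run holds study arm and the "three stratification variables used for randomization (Site, Chronic Pain, and comorbid Alcohol or Marijuana Use) only first". The second run adds whatever was found unbalanced, and the results are compared.
- **Secondary model for days of misuse.** Both versions contain "strata variables and baseline days of misuse without and with additional covariates identified above added".

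The Secondary outcome section confirms that the baseline measure exists: "TLFB will be administered at study enrollment (baseline) and monthly by phone".

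**The concern.** A test of baseline balance in a properly randomised trial tests a null hypothesis known to be true. What it flags is chance, and whether a variable is flagged does not depend on how strongly it predicts the outcome. A prognostic variable outside the stratification set that happens to be balanced is therefore never used, although adjusting for it would sharpen the estimate.

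The second step adds a dependence on the treatment results themselves. Two arm effects are computed and compared, and only then is it settled which one is the primary result. Because similarity is undefined, two analysts following the text faithfully could report different primary estimates from the same data.

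The treatment of baseline opioid misuse is also uneven. It is a fixed covariate for the self-reported secondary outcome, whereas for the primary outcome it is not named at all. At stake are a primary estimate that is not fixed in advance and some power that would cost nothing to obtain.

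**Working it through.** **1. The plan's own figure.** Sample size {14} gives a standardised difference of 0.35, alpha 0.05, power 0.80, 1:1 allocation and a t-test. Sidedness is not stated.

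- Normal approximation, two-sided: n per arm = 2(1.960+0.842)²/0.35² = 128.1, so 129 (258 in total).
- Exact t-test: 129.1, so 130 per arm = **260**, with power 0.803.
- A one-sided test would give 202, which does not fit.
- Dropout: 260/0.80 = 325. Rounded up to a multiple of the 12 strata this is **336**.

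Both figures reproduce. The checks below use 130 per arm and 0.35.

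**2. How often the trigger fires under perfect randomisation.** Let k be the number of baseline variables tested (not given in the document), with tests taken as independent. More than 5% of k must be significant, so at least m = floor(0.05k)+1. The probability is P(Binomial(k, 0.05) ≥ m).

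| k | m | P(trigger) |
|---|---|---|
| 5 | 1 | 1 − 0.95⁵ = 0.226 |
| 10 | 1 | 1 − 0.95¹⁰ = 0.401 |
| 15 | 1 | 0.537 |
| 19 | 1 | 0.623 |
| 20 | 2 | 0.264 |
| 30 | 2 | 0.446 |
| 40 | 3 | 0.323 |

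Below 20 variables, one significant test is enough. The jump from 0.62 to 0.26 between 19 and 20 variables shows how arbitrary the threshold is.

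**3. What the whole rule does to error rates.** Simulation: 20,000 trials per setting, 130 per arm, 10 independent baseline covariates, jointly explaining 20% or 40% of outcome variance (R²; both values are assumptions).

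| | R² = 0.2 | R² = 0.4 |
|---|---|---|
| Type I error, dissimilar = significance changes | 0.044 | 0.040 |
| Type I error, dissimilar = estimate changes by >10% | 0.045 | 0.041 |
| Type I error, smaller p-value always reported | 0.056 | 0.057 |
| Power under the rule (first two readings) | 0.81 | 0.82 |
| Power, same 10 covariates prespecified | 0.87 | 0.95 |

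The first two readings are conservative for a simple reason. An unadjusted test rejects too often when prognostic covariates are unbalanced and too rarely when they are balanced. Adjusting only in the unbalanced trials removes the excess and keeps the shortfall.

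**4. Gain from baseline days of misuse alone.** Let r be its correlation with the primary score, given arm and the stratification variables. The documents do not give r, so 0.2 to 0.5 is assumed. The residual SD is √(1−r²), and power = Φ(0.35/[√(1−r²)·√(2/130)] − 1.960).

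- r = 0: 0.35/0.1240 = 2.822; Φ(0.862) = 0.806
- r = 0.2: 2.822/0.980 = 2.880; Φ(0.920) = 0.821
- r = 0.3: 0.841
- r = 0.4: 0.868
- r = 0.5: 2.822/0.866 = 3.259; Φ(1.299) = 0.903

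The total N giving 80% power falls from 258 (r = 0) to 248, 234, 216 and 194 for r = 0.2, 0.3, 0.4 and 0.5.

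**The case against.** The strongest defence is that the first model is fixed. Site, chronic pain and comorbid alcohol or marijuana use enter whatever any test shows, and Sequence generation {16a} says the last two were chosen because they may affect outcome. Screening is confined to variables already thought prognostic. The rule has no direction: a favourable result is not a criterion, and under Who will be blinded {17a} the analysing biostatistician does not know the group labels. Power under the rule stays at or above the planned 0.80. All of this stands, and it limits the harm. It does not fix in advance which estimate is primary.

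The defence of leaving out baseline misuse also has substance. In the secondary model it is the baseline value of the same measure. The primary score counts missed urine tests as positive and so partly reflects attendance, while the calendar is self-report and open to misreporting. Enrolment comes within three weeks of starting outpatient treatment, so past-month recall may mix days before and during treatment. The omission is therefore a missed opportunity, not a contradiction, and the gain depends on an unknown correlation.

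A reader might draw stronger conclusions that the documents do not support:

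- *That type I error is inflated.* Under two plausible readings it is about 0.040–0.045. Reaching 0.056–0.057 requires picking the more favourable result, which the rule does not provide for.
- *That the primary result has a 40–62% chance of being changed.* Those figures are the chance of a second run for 10 to 19 variables. The reported model changes only if the results then differ.
- *That baseline misuse is barred.* It could enter through the open-ended list if it tested as unbalanced.
- *That adjusted and unadjusted effects must differ because a generalised linear model may be used.* This holds for non-collapsible effects such as odds ratios under a logit link. It does not hold for identity or log links, and the protocol names no logit link.

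**Conclusion.** The point holds in a limited form. Beyond arm and the three stratification variables, the covariates of the primary model are selected by tests that detect only chance, and the model reported is settled by comparing treatment results against an undefined standard. This is a rule the protocol states, not a detail left to a later document.

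The firm consequences are that the primary estimate is not determined until treatment results are in view, and that precision is forgone. With independent tests, the trigger would fire in roughly a quarter to three fifths of perfectly randomised trials, depending on the unstated number of variables. Adding baseline days of misuse would move power from about 0.80 to 0.82 at r = 0.2 and to 0.90 at r = 0.5. These sizes rest on assumed values for k, r and R² and on independence of the baseline tests.

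**What to change.** In section {20a}:

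1. Delete the baseline-test trigger and the rule that chooses between models by similarity of results. Baseline characteristics can still be tabulated by arm.
2. Name one primary model: study arm, site, chronic pain, comorbid alcohol or marijuana use, and baseline days of opioid misuse from the calendar, plus any other prognostic covariates the investigators list by name in advance.
3. Label the model with stratification variables only, and any model adjusted for observed imbalance, as sensitivity analyses that cannot replace the primary result.
4. Apply the same principle, covariates fixed in advance, to the mixed model for days of misuse and to the survival analyses.

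The cost is analysis wording only. The added covariate is already collected at enrolment, and the planned 260 evaluable and 336 enrolled need not change. The change should be made before any outcome comparison by arm is seen.

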## Discussion

We have described our planned protocol for a randomized controlled trial evaluating adjunctive use of smartphone app OptiMAT to improve 6-month outcomes for patients receiving MAT for OUD. We believe that OptiMAT’s use of daily monitoring, personalized feedback, and GPS-driven just-in-time intervention will reduce opioid misuse during this 6-month trial.

Our trial design includes several best practices for RCT methodology, including stratification of study arm assignment by key study variables suspected to influence outcome (comorbid pain interference and comorbid use of alcohol or marijuana); reliance on the Treatment Effectiveness Score for primary outcome of negative urinalysis test; data safety monitoring; and inclusion of secondary outcomes for participants who discontinue MOUD treatment. We acknowledge that study confounds may still arise despite these best practices and provide an adaptable statistical plan that can be tailored to the specific data properties of the resulting dataset (e.g., adjusting for non-normal distributions and patterns of missing data).

We additionally provide subanalyses for evaluating the OptiMAT features and usage patterns that best predict 6-month outcomes. These subanalyses seek to identify the mechanisms by which app-based interventions promote positive outcomes, and thus identify the critical components for future app interventions.

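### The primary model depends on a normality check that a bounded urinalysis score will very likely fail, which leaves the primary effect measure unfixed and possibly different from the mean difference used for the sample size

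*Protocol article*

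**What the plan says.** Protocol article, Analyses of primary and secondary outcomes (under {20a}): "General linear or generalized linear models (GLMs) will be used to examine associations between study arms and primary outcome" at six months, with the choice between the two made "depending on whether the outcome is normally distributed or not". The check itself is described only in general terms: "Distributions of outcome variables will also be assessed using appropriate tests and visual graphs". No threshold is given, and the non-normal branch has no family, link or effect measure.

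Primary outcome (under {12}): "We will calculate percent negative urinalysis tests out of total possible urinalysis tests", and "TES treats missed urinalysis tests as positive urinalysis results".

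Sample size {14}: the calculation is "for comparisons of the mean difference between the two groups using independent" t-test, with a standardized difference of 0.35, type I error 0.05 and power 0.80. It gives 260 participants, raised to 336 enrolled.

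Discussion: the authors count it as a strength that they "provide an adaptable statistical plan that can be tailored to the specific data properties of the resulting dataset".

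**The concern.** A primary analysis should fix in advance what is estimated. Here the data decide. If the score looks normal, the treatment effect is a difference in mean percentage. If not, it is whatever the chosen generalized linear model reports, which under the usual logit or log link is an odds ratio or a ratio of means.

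The non-normal branch is the one to expect. The score cannot leave the range 0 to 100, participants who stop treatment are pulled toward 0 because missed tests count as positive, and sustained abstainers gather near 100. So the rule probably sends the primary analysis away from the quantity that justified the sample size and into a branch the article does not define. By contrast, for monthly days of misuse the same section expects skew and names Poisson or negative binomial in advance.

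**Working it through.** **1. The plan's own figure.** Inputs from Sample size {14}: δ = 0.35, α = 0.05 (sidedness not stated), power 0.80, 1:1 allocation, 20% drop-out, 12 cells.

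- Normal approximation, two-sided: n per arm = 2(1.960 + 0.842)² / 0.35² = 128.2, so 129 per arm and 258 in total.
- Exact noncentral t, two-sided: 130 per arm, 260 in total, power 0.803. One-sided (normal approximation) gives 202 and does not match.
- Enrolment: 260 / 0.80 = 325. Since 325 / 12 = 27.1, rounding up gives 28 × 12 = 336.

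The stated figures are reproduced, and they rest on a two-sided test of a mean difference.

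**2. What a change of scale means.** The article gives no standard deviation or control mean. Assume an SD of 25 to 35 points and a control mean of 40% to 70%.

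- Mean difference: 0.35 × 25 = 8.8 points to 0.35 × 35 = 12.2 points.
- Example with control mean 50% and SD 30: 0.35 × 30 = 10.5 points, so the other arm has 60.5%. The odds ratio is (0.605/0.395)/(0.50/0.50) = 1.53, and the ratio of means is 0.605/0.50 = 1.21.
- Over the whole range: odds ratio 1.42 to 1.99, ratio of means 1.12 to 1.31.

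One standardized difference thus maps to a spread of ratios that depends on the control mean and SD.

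**3. Does the check fail, and does failure matter?** Simulated trials with no effect, 130 per arm, 26 possible tests each, participant rates from beta distributions, some participants stopping early with later tests scored positive. All of these settings are assumptions. Analyses were unadjusted, and normality was judged by Shapiro-Wilk at 5%.

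| Rates; share stopping early; runs | Normality rejected | Comparison of means | Overdispersed logit | Uncorrected binomial on counts |
|---|---|---|---|---|
| Beta(0.5,0.5); 0%; 2000 | 100% | 5.8% | – | 59.5% |
| Beta(1,1); 0%; 2000 | 100% | 5.2% | – | 50.8% |
| Beta(2,2); 0%; 2000 | 99.95% | 5.4% | – | 41.3% |
| Beta(1,0.6); 0%; 2000 | 100% | 5.1% | – | 54.5% |
| Beta(3,2); 20%; 3000 | 100% | 4.5% | 4.6% | 43.0% |
| Beta(3,2); 40%; 3000 | 100% | 4.8% | 4.8% | 45.1% |
| Beta(0.8,0.6); 40%; 3000 | 100% | 5.1% | 5.1% | 57.6% |
| Beta(6,4); 0%; 1000 | 93.5% | 6.2% | – | – |
| Beta(10,10); 0%; 1000 | 67.3% | 4.9% | – | – |

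The last four columns are rejection rates. The Monte Carlo standard error at a true 5% is √(0.05 × 0.95 / runs): 0.7 points for 1000 runs, 0.5 for 2000 and 0.4 for 3000. The last two rows are therefore the least precise.

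**4. Power of the comparison of means.** With a true difference of 0.35 SD and 40% stopping early (4000 runs each), power was 80.1% for Beta(3,2), where means are 48.0% and 57.2%, and 80.8% for Beta(0.8,0.6), where means are 45.7% and 57.2%. Non-normality does not cost the planned power in these settings.

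**5. Effect of the rule itself.** In five 1000-run scenarios, using the linear model when Shapiro-Wilk passed and an overdispersed logit model when it failed moved the rejection rate by 0.1 point each time (for example 6.2% to 6.3%, and 4.9% to 5.0%). In further runs with 8, 12 or 26 tests, the two models reached the same decision in at least 99.5% of trials.

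**6. Fewer tests.** The article says testing thins out as patients progress. The uncorrected binomial's type I error was 27% to 45% with 12 tests and 21% to 34% with 8.

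**The case against.** **The analysis plan may settle this.** Family and link are commonly left to an analysis plan, which is not shown here, and their absence alone is no fault. But the article does more than stay silent: it states a selection rule for the primary analysis, and an analysis plan that followed it would inherit the rule.

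**The analyst is blinded.** Who will be blinded {17a} keeps the biostatistician unaware of group labels. That limits choosing a model for its result, and nothing in the document suggests such choosing. It does not fix the effect measure.

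**A generalized linear model need not change the estimand.** True. With an identity link, or with fitted means compared between arms, it would still give a mean difference. The article names neither, so the departure is likely but not established.

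**If failure is nearly certain, the branch is effectively fixed.** Partly so, but the branch it is fixed to has no stated effect measure. Nor is failure certain: the most favourable scenario was rejected in 67.3% of runs, and the article also relies on graphs.

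**The stronger reading.** A reader might infer that the rule inflates the trial's type I error to 40% or 60%. The document does not support that. Those figures belong to a binomial model treating every test as independent. The article analyses a percentage and never proposes pooling test counts. An overdispersed model held 4.6% to 5.1%.

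**Conclusion.** The point holds as a defect in how the primary effect measure is fixed. The article powers the trial on a difference in means, then lets a normality check decide whether that difference is what gets estimated. For a bounded score with missed tests counted as positive, the check is very likely to fail: 99.95% to 100% in the first seven tabulated scenarios, falling to 67.3% in the most favourable one. The check also protects nothing at about 130 per arm, since the comparison of means is close to nominal without normality.

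Two further inferences should be resisted. The planned sample size is not wrong; it is reproduced. And the significance decision would not be unreliable under a sound non-normal model, which agrees with the linear test almost always. Inflation of about 27% to 60% (12 to 26 tests) is a hazard the open wording permits, not an expected result.

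All simulated figures rest on assumed beta distributions, test counts and stopping rates, and on unadjusted analyses with equal numbers of possible tests. The scale conversions rest on an assumed SD and control mean.

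**What to change.** Delete the normality condition from {20a}. State instead that the primary analysis is the difference in mean TES between arms from a linear model with arm and the three stratification factors listed there (site, chronic pain, comorbid alcohol or marijuana use), with heteroskedasticity-robust standard errors, whatever the distribution of the score. Keep an overdispersed binomial or beta-binomial model as a sensitivity analysis.

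Deleting the condition alone would leave two other routes open: the Bayesian fallback, which reports ratios of means on the log scale, and the models rerun with unbalanced covariates added. The same sentence should therefore say that the difference in mean TES stays the primary effect measure if either is run.

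Cost: a sentence or two, no new data, and no change to 260 evaluable or 336 enrolled. The one small drawback is that a linear model can give fitted values outside 0 to 100.
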